## Abstract

**Background:**

Continuous medical education is traditionally reliant to a large extent on self-directed learning based on individuals' perceived learning priorities. Evidence suggests that this ability to self-assess is limited, and more so in the least competent. Therefore, it may be of benefit to utilise some form of external assessment for this purpose. Many diabetes educational programmes have been introduced, but few have been assessed for their benefit in a systematic manner. As diabetes is an increasingly prevalent disease, methods for the dissemination and understanding of clinical guidelines need to be explored for their effectiveness. This paper describes the study design of a randomised controlled trial to evaluate the effectiveness of using an interactive online Diabetes Needs Assessment Tool (DNAT), that builds a learning curriculum based on identified knowledge gaps, compared with conventional self-directed learning. The study assesses the effect of these interventions on health professionals' knowledge of diabetes management, evaluates the acceptability of this process of learning and self-reported changes in clinical practice as a result of this novel educational process.

**Methods:**

Following a baseline assessment, participants will be randomised to undergo a 4-month learning period where they will either be given access to the diabetes learning modules alone (control group) or a Diabetes Needs Assessment Tool (DNAT) plus the diabetes learning modules (intervention group). On completion of the DNAT, a personalised learning report will be created for each participant identifying needs alongside individualised recommendations of the most appropriate learning modules to meet those requirements. All participants will complete a Diabetes Knowledge Test before and immediately after the allocated learning and the primary outcome will be the state of knowledge at 4 months. Learners will also be surveyed immediately after the learning period to assess the acceptability of the learning formats and the perceived usefulness and usability of the materials. After a further month, all learners will receive a series of questions to evaluate self-reported changes in clinical practice as a result of this educational experience and asked to include specific examples of any changes in their diabetes care practice.

**Trial registration:**

Current Controlled Trials ISRCTN67215088

## Background

Doctors need ongoing learning in order to stay up to date. Therefore, they need a method of continuous professional development that is convenient and practical which enables them to meet their personalised needs. Online learning provides learners the opportunity to personalise their learning, for example, the order in which they read material, the speed of their learning, where and when they choose to learn.[1] In agreement with previous reviews, [1-3] a more recent systematic review and meta-analysis [4] of the effects of internet-based learning involving health professionals in a wide range of learning contexts and clinical areas reaffirmed that internet-based learning can be as effective as more traditional methods of learning. Major positive effects were found compared with no intervention for both knowledge outcomes, skills, learner behaviour and patient effects. This suggests that future research should focus only on direct comparisons between the different types of internet based interventions.

Continuous medical education is traditionally reliant to a large extent on self-directed learning based on the individual's perceived priorities for learning. Evidence suggests that this ability to self-assess is limited, and more so in the least competent.[5] There is also evidence that practitioners prefer to focus on topics which they are already familiar with and avoid less familiar topics.[6] Current thought is that interactive CME activities that help individuals recognise a "teachable moment" and an opportunity for learning can help encourage engagement in the learning and motivate learners to pursue the activity.[7] While there are methods to help you discover your knowledge and skills gaps, there is no one definitive methodology. Using a variety of methods often gives a better overall view.[8] Therefore it may be of benefit to have some form of formal external assessment.[9] Exclusive reliance on a formal needs assessment might discourage creativity and professionalism,[10] but it could be an important part of the process.

Miller [11] has defined the ideal stages of the development of physician skills. The first level is "declarative knowledge" i.e. the acquisition and interpretation of facts. This is followed by "procedural knowledge" where individuals can describe how to do something but may not be able to actually do it. The third level is about demonstrating that you know how to do what you have learned, i.e. developing "competence". The fourth level involves individuals using the competence they have developed in their actual clinical practice ("performance"). Moore et al's[7] conceptual framework of an approach to continuous planning and assessment in continuing medical education builds on Miller's[11] model to incorporate an assessment on improvements in patients' health status and finally the health status of the population. However, Curran and Fleet [12] reviewed the types of outcome measures used in evaluative research in web-based CME and found that most research has focused on participants' satisfaction and not on change in clinical practice or impact on patient and health outcomes. While assessing the effect on patient's health status can be hampered by ethical constraints in gaining access to data,[7] assessing whether learners have tried to use their competence in practice seems crucial in an assessment of the effectiveness of a learning intervention.

As diabetes is an increasingly prevalent disease, methods for the dissemination and understanding of clinical guidelines need to be explored for their effectiveness. In educational research on diabetes much of the focus has been on the mode of delivery of the education with mixed results from traditional method of small group teaching to larger structured learning programmes.[13,14] Internet-based interventions in diabetes have been shown to increase guidelines knowledge[15,16] and compliance.[17] Many education programmes have been examined but few in a systematic manner and across wide geographic areas involving large numbers.

There is no previous randomised controlled trial (RCT) evaluating the effectiveness of different formats of administering online learning materials in the field of diabetes on knowledge and subsequent change in clinical practice. Therefore, we have designed an RCT of two different formats of online learning for health professionals, i.e. an interactive online learning tool with access to relevant learning modules (active intervention group) compared with access to relevant learning modules alone (control group) to assess effectiveness in terms of diabetes knowledge, satisfaction and self-reported change in clinical practice. We describe here the design of this randomised controlled trial.

## Methods

### Design

This is a randomised controlled trial to evaluate the effectiveness of using an online interactive learning tool, Diabetes Needs Assessment Tool (DNAT), in conjunction with a learning management system (LMS) to improve health professionals' knowledge of how to manage diabetes; to evaluate the acceptability of this process of learning; and self-reported changes in clinical practice as a result of this educational process.

### Participants

Volunteers will be recruited through targeted emails and advertisements inviting English and German speaking practicing doctors and nurses to take part in an educational research project. Interested individuals will be asked to complete an eligibility questionnaire online (see inclusion/exclusion criteria) and those deemed eligible will be given the opportunity to register for the trial. We have produced two parallel websites, one for English speaking participants and the other for German speaking participants. Participants are able to choose whether they want to receive the materials in English or German.

Participants will be informed that the time spent on learning activities for the project will contribute to their Continuing Professional Development (CPD) requirements and that they will receive a personalised certificate of learning on completion of the course. Participants will be told that they will receive their test results and correct answers, and access to the most effective learning package at the end of the study free of charge. In addition, a choice of access to one of three BMJ knowledge related products (English speaking participants) and some QUAIME AG online learning modules (German speaking participants) will be provided.

#### Inclusion and exclusion criteria

On registering for the study, potential participants will be asked a series of screening questions ensuring that only eligible participants are recruited i.e. participants must be either English or German speaking practising doctors or nurses managing at least one patient with diabetes per week. Note – German nurses, except diabetes nurses and assistants for family physicians, will be excluded from taking part as they are not licensed to receive training where information about pharmacological treatment is included.

#### Ethical approval and trial registration

The Research Ethics Committee for Wales confirmed that the study does not require full ethical review (personal communication 07 January 2009). The research will be carried out in compliance with the Helsinki Declaration. All participants will be asked to give their consent to take part in registration. The trial was registered with Current Controlled Trials before any participants were recruited (Current Controlled Trials ISRCTN67215088). The study adheres to the Good Publication Practice guidelines for pharmaceutical companies.

### Assessments and procedures

All assessments, learning materials, and surveys will be administered to participants online at the study website. Participants will be asked to give their consent to take part in a randomised controlled trial designed to test the effectiveness of different learning materials and methods and will be informed that they will be required to use the online learning materials for at least five hours during the 4-month learning period. Figure 1 is a schematic representation of the key components of the trial.

**Figure 1 F1:**
[figure not shown]
**Schematic representation of components of the intervention and assessment points**.

Once registered, participants will be asked to complete the first Diabetes Knowledge Test before being randomised to a study group. At the start of the 4-month learning period they will be directed to their randomly allocated learning materials. Learners in both groups will receive the same six automated reminders to look at the learning materials during the learning period (4, 8, 10, 12, 14, and 16 weeks after the start of the learning period). The intervention group will not be reminded to look specifically at the DNAT during the learning period.

Immediately after the learning period, access to the learning materials will be closed and all learners will be asked to complete the second Diabetes Knowledge Test (Test B) and the Acceptability Survey. After a further month, all learners will be asked to complete the Practice Change Survey. The administration of these tests and surveys will be automated so all learners receive them at the same interval after receiving the learning materials. Non-responders will be emailed a series of reminders to complete the test and survey. Learners who do not complete the Diabetes Knowledge Test B and/or the Acceptability Survey will still be followed up and asked to complete the Practice Change Survey.

### Data collection and handling

Baseline data will be collected automatically when participants register online for the study. The following information will be recorded in the database: health professional role (doctor or nurse), preferred language to receive study materials (German or English), years since qualification, baseline Diabetes Knowledge Test score and whether they are registered users of the webservice univadis^® ^and/or BMJ Learning. Baseline information will be used to check comparability between study arms. Diabetes Knowledge Test B scores and follow-up questionnaires will be automatically collected online. Anonymised and blinded data will be exported in a format appropriate for statistical analysis.

### Interventions

Participants will not be told which group they have been allocated to. All participants will be given access to the same online Diabetes Learning Modules (see below) on a Learning Management System (LMS). An LMS is a technical platform which tracks all user behaviour including how long and how often materials are used, and also ensures that learners follow the materials in a fixed sequence. In addition, the intervention group will be administered a novel interactive learning tool, the DNAT. A link tracking system will capture which resources individual learners visit during the learning period. As the learners progress with the modules they will also be prompted to indicate which they completed and estimate the time they spent using them.

#### Diabetes Learning Modules

Participants in both groups have online access to the same Diabetes Learning Modules on the LMS. All the content of these learning modules is applicable to European practice and material comes from BMJ Learning, Excerpta Medica, a division of Elsevier Health Sciences, and the International Diabetes Federation and Elsevier Health Sciences. The modules include current evidence-based guidelines (particularly those of the European Association for the Study of Diabetes and the European Society of Cardiology) on diabetes, pre-diabetes and cardiovascular disease; important clinical areas and common difficulties in practice (Type 1, Type 2, diabetes in pregnancy and secondary causes of diabetes).

#### Diabetes Needs Assessment Tool (DNAT)

The DNAT is a new web-based diabetes interactive learning tool. It is a computerised adaptive test comprised of clinically rich case problems developed by a group of diabetologists/educationalists. The 253 DNAT test items have already been validated through use with a large number of learners with a range of ability registered on BMJ OnExamination. The items cover six categories: Principles of Diabetes (53 items), Lifestyle (49 items), Drug Treatment (64 items), CVS/Macrovascular (34 items), Acute Complications (21 items), Microvascular Complications (32 items). The DNAT can be completed over several sessions if required and takes the learner approximately 90 to 120 minutes to complete. Not all learners will see the same questions as the test adapts to knowledge level as individuals complete it. On completion of the DNAT, a personalised learning report is created for each learner identifying learning needs alongside individualised recommendations of the most appropriate Diabetes Learning Modules to meet those needs. At any stage this personalised report can be viewed listing the performance of the learner at that point.

### Outcome measures

#### Primary Outcome measure

##### Diabetes Knowledge Test

The Diabetes Knowledge Test contains 20 multiple choice questions (in the format of single best answer out of five possible options). There are two versions of the Diabetes Knowledge Test – Test A and Test B. All learners will receive the same baseline Diabetes Knowledge Test (Test A) prior to randomisation. Test B is a slightly different test of equal difficulty to be administered at the end of the learning period. The primary outcome will be Diabetes Knowledge Test scores at four months. Note-while the knowledge tests contain 20 items, only 19 items will be used in the knowledge test scores as one of the items in each test is a "rogue" item not on diabetes.

The Diabetes Knowledge Tests were developed from the same large pool of calibrated items as the DNAT but there is no overlap between the DNAT and the knowledge tests.

#### Secondary outcomes

##### Acceptability Survey

Immediately after the learning period, all learners will be administered a survey containing a series of questions about their level of satisfaction with the materials received and the acceptability of the learning formats. They will be asked about the perceived usefulness and usability of the materials. Participants in the intervention group will be asked additional specific questions about the acceptability of the DNAT.

##### Practice Change Survey

Five months after the start of the learning period, all learners will be administered a series of questions on self-reported changes in clinical practice as a result of the learning experience. They will be asked to give specific examples of any changes in their diabetes management. This will be used as an indicator of the transference of competence into clinical behaviour.

### Randomisation and allocation concealment

Eligible registered participants who complete Diabetes Knowledge Test A will be randomised to the control and intervention groups of the study. Optimal allocation with a ratio of 1:1 will be used. Randomisation will be balanced for language (English or German), ability (based on Diabetes Knowledge Test A scores), doctor vs nurse, and number of years since qualified at medical or nursing school, and whether they are registered users of the webservice univadis^® ^and/or BMJ Learning, using a minimisation technique.[18] The total sample of health professionals recruited will be divided into blocks of 24 and within each block a process of optimal allocation will be undertaken. This involves obtaining all possible allocations and calculating a balance statistic.[19] 1000 allocations with the greatest degree of balance will be identified and passed to a statistician within the South East Wales Trials Unit (SEWTU) at Cardiff University, (who is independent of the trial) who will randomly select a single allocation for each block. This will then be returned to the trial statistician (RP) and the study database manager informed of the allocations.

### Blinding

All outcome measures are tests and self-report surveys and will be administered automatically online. All data will be held in the online database. The statistical analysis of the trial data will be conducted by an independent statistician at SEWTU blinded to the group allocation of participants until the analyses are completed.

### Translation of study materials

All study materials were originally developed in English and subsequently translated into German. All recruitment and marketing material, communication to research participants, instructions on how to participate and website information were translated by an independent company and this was then reviewed by one of the bilingual members of the study team. The independent companies were selected by BMJ Group and contracted to do the work. While these companies do regular work for the pharmaceutical industry, they do not regularly work for MSD. The company did the work under their own editorial principles and MSD had no influence on the work that they produced. The DNAT and Diabetes Knowledge Tests underwent a more rigorous multi-step process. Content was translated by an independent company (from English to German) and the translated text from this company was then sent to a second independent company for proofing. The text was then medically reviewed by bilingual members of the research team and the texts finalised.

### Sample size

We estimated that for a moderate effect size of 0.4 we needed a minimum of 100 participants in each arm (at a significance level of 0.5 and power of 80%). For an effect size of less than that, e.g. 0.3 the sample size increases to 176 per group. These needed to be inflated to account for drop out.

Since recruitment was to take place via online and print advertisement and registration, recruitment rates, learning material uptake and drop out were unknown, we decided to allow up to 1000 participants per country to complete the registration and baseline test until the cut off date for study recruitment. Obtaining a larger sample size than stated above will provide greater power for smaller effect sizes and allow the country subgroup analyses to have more power.

### Statistical Analysis

All data will be checked during data cleaning for outlier data. Range checks from the online data collection will eliminate any out of range data. Any observed outliers will be checked with the database management team. Intention to treat analysis will be carried out for the primary analysis. Participants will be encouraged to complete Diabetes Knowledge Test B even if they have not spent as much time learning as they had planned. Complete case analysis will be used as a secondary analysis.

Summary statistics on participant assessment, eligibility, recruitment, withdrawal and dropout will be collated for both arms of the trial and form the CONSORT flow diagram for clinical trial reporting. The primary analysis will use Analysis of Covariance (ANCOVA) to compare the follow-up diabetes knowledge test scores between trial arms adjusting for baseline score as a covariate. This analysis makes distributional assumptions about the data and these will be checked prior to analysis. Variables used in the balancing algorithm will also be considered for inclusion as covariates. Secondary outcome analysis will compare the acceptability and practice change outcomes between trial arms. T-tests and Chi square tests will be used where appropriate for questionnaire items.

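### Survey items are to be compared with unadjusted t-tests and chi-square tests although allocation is balanced on five recorded baseline factors, so standard errors are too large and the tests conservative

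*Protocol article*

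**What the plan says.** The Statistical Analysis section of the protocol article deals with the surveys in two sentences: "Secondary outcome analysis will compare the acceptability and practice change outcomes between trial arms", followed by "T-tests and Chi square tests will be used where appropriate for questionnaire items". The Acceptability Survey section says that "all learners will be administered a survey containing a series of questions about their level of satisfaction with the materials received". The Practice Change Survey section says that "all learners will be administered a series of questions on self-reported changes in clinical practice as a result of the learning experience". Neither section gives the number of items or their response format.

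The allocation section says "Randomisation will be balanced for language (English or German), ability (based on Diabetes Knowledge Test A scores), doctor vs nurse, and number of years" since qualification, and adds whether the participant is a registered user of the two web services. The section on data collection and handling lists all five of these variables among the recorded baseline data.

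The primary analysis is treated differently. It is an ANCOVA to "compare the follow-up diabetes knowledge test scores between trial arms adjusting for baseline score as a covariate". The sentence "Variables used in the balancing algorithm will also be considered for inclusion as covariates" stands in the text on that analysis, before the secondary outcomes are introduced.

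**The concern.** The trial takes trouble to make the arms alike on five factors. When such factors predict an outcome, balance reduces the true variability of the difference between arms. A t-test or chi-square test does not know this: it computes its standard error as if allocation had been simple randomisation. The reported uncertainty is then larger than the real one, intervals are too wide, and real differences are harder to detect.

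The plan recognises the principle for the knowledge score and does not carry it over to the surveys. Self-reported practice change is the trial's indicator that knowledge passes into clinical behaviour, so avoidable imprecision there has some cost, although the outcome is secondary.

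**Working it through.** The article gives no figure for the precision of the survey comparisons, so there is none to reproduce. The check asks how large the effect could be.

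**Inputs**
- Tests for survey items: t-test and chi-square, without covariates (Statistical Analysis).
- Allocation: 1:1, balanced on five factors (Randomisation and allocation concealment).
- Share of an item's variance explained by the balancing factors, R²: not given. Assumed 0.10 to 0.20, with 0 as the no-effect case.
- Test level: 0.05 two-sided. The Sample size section prints 0.5, but its 100 and 176 per arm follow from 0.05 two-sided (t-based 99.1 and 175.4, rounded up). A level of 0.5 two-sided would give 29 and 52.
- Illustration for power: effect 0.3 SD with 176 per arm. The article gives these figures for its sample size; they are borrowed here only to show scale.

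**Standard error.** With balance close to perfect, the true variance of a mean difference is (1 − R²) times the value that the t-test assumes. The unadjusted standard error is therefore too large by the factor 1/√(1 − R²):
- R² = 0.10: 1/√0.90 = 1.054, about 5% too large.
- R² = 0.20: 1/√0.80 = 1.118, about 12% too large.

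In terms of interval width, this is like discarding 10% to 20% of respondents.

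**Type I error.** The true rate of the nominal 5% test is 2 × [1 − Φ(1.96/√(1 − R²))]:
- R² = 0: 5.0%.
- R² = 0.10: 2 × [1 − Φ(2.066)] = 3.9%.
- R² = 0.20: 2 × [1 − Φ(2.191)] = 2.8%.

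**Power in the illustration.** 0.3/√(2/176) = 2.814. Unadjusted power is Φ((2.814 − 1.96)/√(1 − R²)); adjusted power is Φ(2.814/√(1 − R²) − 1.96).
- R² = 0.10: 81.6% unadjusted, 84.3% adjusted.
- R² = 0.20: 83.0% unadjusted, 88.2% adjusted.

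These are limits under perfect balance, and they hold for differences in means. They do not carry over to odds ratios, where covariate adjustment changes the quantity being estimated and does not shrink its standard error in this way.

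**The case against.** Several arguments count against the point.

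- **R² is assumed.** Both surveys are first given after the learning period, so they have no baseline value of their own, and nothing in the article shows that knowledge score or years since qualification predicts satisfaction or practice change. This stands: the direction is certain only if the factors matter at all, and the size is unknown. If R² is near zero, adjustment gains almost nothing, and with samples of this size it also costs almost nothing.
- **The error is in the safe direction, and the sample may be large.** Up to 1000 registrants per country are allowed. A standard error 5% to 12% too large on secondary items may then matter little. This also stands, and it is why the point is minor.
- **The wording leaves room, and an unseen analysis plan may say more.** It is true that the choice of test is qualified. The qualification most naturally chooses between the two named tests, however, and neither admits covariates. The article states a method here, so the point does not rest on silence.
- **Responders only.** One might add that survey response may depend on language or profession. By itself that does not bias the comparison between arms; it would have to differ by arm as well. It is not used here.

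A reader might also infer that item-by-item testing makes a chance significant survey item likely, and that the plan is at fault for naming no headline item or multiplicity rule. The article does not support this. It gives neither the number of items nor their correlation. At 5% per item, a chance above 50% of at least one false positive needs at least 14 independent items (1 − 0.95¹⁴ = 51%), or about 30 items correlated at 0.5. With 5 to 10 items correlated at 0.5 to 0.7, the chance is about 15% to 29%. Omitting the balancing factors lowers these rates and cannot cause false positives. Rules for headline items and multiplicity are commonly left to the analysis plan, which is not shown.

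**Conclusion.** The concern holds as a minor point about precision. The stated tests for the survey items ignore balancing factors that are already in the database, and they are out of line with the adjusted primary analysis. If those factors explain 10% to 20% of an item's variance, the standard error of a mean difference is overstated by about 5% to 12%, and the true type I error is about 3.9% to 2.8% in place of 5%. Both figures rest on the assumed R², on near-perfect balance among those analysed, and on a 0.05 two-sided level. The conclusion does not extend to an excess of false-positive items.

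**What to change.** In the Statistical Analysis section, replace the t-tests and chi-square tests for survey items with regression on trial arm, with Test A score, language, profession, years since qualification and registered-user status as covariates. Report an adjusted mean difference for graded or score items and an adjusted marginal risk difference for yes/no items, each with a 95% confidence interval. These measures are preferable to odds ratios because adjustment leaves their meaning unchanged.

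The cost is a change of wording and slightly more programming. No new data are needed, since all the covariates are collected at registration and at the baseline test.
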